# Early versus late initiation of renal replacement therapy in critically ill patients with acute kidney injury (The ELAIN-Trial): study protocol for a randomized controlled trial

**DOI:** 10.1186/s13063-016-1249-9

**Published:** 2016-03-18

**Keywords:** Critically ill patients, Renal replacement therapy, Acute kidney injury, Clinical trial

## Abstract

**Background:**

Acute kidney injury remains a common complication in critically ill patients and despite multiple trials and observational studies, the optimal timing for initiation of renal replacement therapy is still unclear. The early versus late initiation of renal replacement therapy in critically ill patients with acute kidney injury (ELAIN) study is a randomized, single-center, prospective, two-arm, parallel group trial to reduce mortality in patients with severe acute kidney injury. We describe the study design and discuss aspects of the need for a trial in this patient cohort.

**Methods/design:**

Our plan is to randomize critically ill patients with acute kidney injury to ‘early’ or ‘late’ initiation of renal replacement therapy according to stage 2 and 3 of the KDIGO classification using a specific trial protocol. We plan to guide data collection and analysis using pre-existing definitions and testing. The primary endpoint is overall survival in a 90-day follow-up period. Secondary endpoints include 28-day, 60-day, 90-day and 1-year all-cause mortality, recovery of renal function, ICU and hospital length-of-stay. The primary analysis will be an intention-to-treat analysis; secondary analyses include treated analyses. We will also specify rules for handling data and determining outcome.

**Discussion:**

Several challenges for study design and execution can be seen in our trial, and it should generate results that will inform and influence the practice of renal replacement therapy in critically ill patients with acute kidney injury.

**Trial registration:**

German Clinical Trials Register: DRKS00004367 (www.germanctr.de); 28 May 2013.

**Electronic supplementary material:**

The online version of this article (doi:10.1186/s13063-016-1249-9) contains supplementary material, which is available to authorized users.

## Background

Acute kidney injury (AKI) is a well-recognized complication of critical illness with an important impact on morbidity and mortality [1, 2]. Despite substantial advances in our knowledge of the management of critically ill patients, mortality associated with AKI remains high [3–5]. Renal replacement therapy (RRT) causes a considerable escalation in the complexity of treatment, has inherent risks for adverse effects and increases cost of care for those with severe AKI. Although RRT is a key component of modern critical care, several fundamental principles, including the optimal timing of RRT initiation, remain unclear [6].

Although there has been interest in the timing of RRT initiation, a lack of consensus regarding the definition and stages of AKI, until recently, has limited progress. In addition, studies have used various arbitrary definitions for ‘early’ and ‘late’ initiation instead of using classification systems for AKI.

A retrospective study assessed the effect of timing of initiation of RRT on outcome in patients with posttraumatic AKI [7]. Serum BUN served as a surrogate marker to determine early versus late initiation of RRT. Survival was 20 % in the late group and 39 % in the early group (*p* = 0.041). Two prospective multicentre observational studies [8, 9] demonstrated higher mortality, longer hospital stay, longer duration of RRT and higher dialysis dependence in the late group. Bagshaw et al. [8] stratified early and late by median urea and serum creatinine at the time RRT was started and demonstrated no significant difference between late and early initiation of RRT using serum urea as surrogate marker (63.4 % vs. 61.4 %, *p* = 0.48). When stratified by creatinine, late RRT was associated with lower mortality (53.4 % vs. 71.4 %, *p* < 0.0001). However, for timing relative to ICU admission, late RRT was associated with higher mortality rates (72.8 % vs. 59 %, *p* <0.001). Shiao et al. [9] divided patients into early (RIFLE-0 or -Risk) and late (RIFLE-Injury or -Failure) RRT by RIFLE criteria and found significantly higher hospital mortality in the late group (74.5 % vs. 43.1 %, *p* = 0.002). A multicentre observational study analyzed data on timing of initiation of RRT based on the median BUN at the time of initiation of RRT [10]. No significant survival benefit in patients receiving early RRT could be demonstrated (survival 59 % late vs. 65 % early, *p* = 0.09). Unfortunately, these observational studies are limited to patients who had received RRT but excluded patients with AKI that had never received RRT. Recently, the Randomized Evaluation of Normal versus Augmented Level of Replacement Therapy (RENAL) study investigators published a subgroup analysis of the RENAL trial testing the effect of earlier commencement of RRT on the outcome of critically ill patients with AKI using RIFLE-Injury as surrogate marker [11]. Earlier initiation of RRT relative to RIFLE-Injury AKI did not show significant graded elevations in the risk of death with progressively delayed RRT. Recently, three meta-analyses suggest that earlier initiation of RRT in critically ill patients with AKI might be associated with a survival benefit [12–14]. However, the studies were heterogeneous and of variable quality.

All of these studies used creatinine, BUN and urine output according to the AKI classification systems to initiate RRT. However, these are functional markers and none of them can predict progression of renal injury and the need for renal replacement therapy [15, 16]. Therefore, in earlier prospective randomized trials some patients received RRT, although these patients might have recovered from AKI without RRT. Lately, research on AKI has focussed on new biomarkers for early detection of AKI and worsening of renal function, making them applicable for initiating RRT [17, 18]. Therefore, a prospective, randomized trial combining functional and damage markers is needed to provide evidence for the best timing of RRT in critically ill patients with AKI.

## Methods/design

The early versus late initiation of renal replacement therapy in critically ill patients with acute kidney injury (ELAIN) study is a randomized, single-centre, two-arm, parallel group trial of different RRT implementation strategies for critically ill patients with AKI. Institutional review board approval was obtained from the Research Ethics Committee of the Chamber of Physicians Westfalen-Lippe and the Westfalian Wilhelms University of Münster (2012-426-f-S), Germany, and the trial is registered in the German Clinical Trials Register (DRKS00004367). The overall study flow is summarized in Fig. 1.

**Fig. 1 Fig1:**
[figure not shown]
Trial workflow. Patients will be identified for recruitment by screening all patients receiving care in the ICU on a daily basis. Before enrolment, the fluid status is analyzed in cooperation with the attending physicians and optimized if necessary. After optimization is ensured, informed consent is obtained and the patient will be registered by randomization. Before initiating RRT, laboratory tests will be performed and different variables will be documented. In the ‘early’ group, RRT will be initiated immediately after randomization, whereas initiation of RRT in the ‘late’ group will be started only after reaching stage 3 of the KDIGO classification and/or if absolute indications for RRT are present. Patients randomized to ‘late’ but never reaching stage 3 will remain in the ‘late’ group for purposes of analysis. Laboratory tests will be analyzed and variables relevant for the assessment of illness severity will be recorded on day 1 to day 21, day 28, day 60, day 90 and 1 year

### Patient population

We plan to enrol 256 adult patients (age 18–90 years) fulfilling the inclusion criteria with written informed consent. If the patient is unable to provide informed consent, the legally authorized representative will be asked and in his/her absence a declaration for inclusion in an emergency situation is to be signed by a consultant physician who is not involved in the study and who is independent of the investigational team. Patient or legally authorized representative informed consent will be obtained as soon as possible. No patient will be excluded from the study on the basis of gender, race or ethnicity. Patients will be identified for recruitment by screening patients receiving care in the critical care units of our centre on a daily basis.

### Inclusion criteria

All patients are eligible if they fulfill all inclusion criteria and no exclusion criteria. The inclusion criteria are as follows:Kidney Disease: Improving Global Outcomes (KDIGO) stage 2 (two-fold increase in serum creatinine from baseline and/or urinary output <0.5 ml/kg/h ≥12 h) (Table 1) despite optimal resuscitation: a) optimizing intravascular volume (fluid resuscitation: pulmonary artery occlusion pressure/central venous pressure of >12 mmHg, stroke volume variation <12 % in ventilated patients); b) optimization of cardiac index (>2.6 l/min per square meter); c) hemodynamic optimization (mean arterial pressure >65 mmHg); and d) normalizing intra-abdominal pressure (<15 mmHg);

**Table 1 Tab1:** Staging of acute kidney injury using KDIGO recommendations

Stage	Serum creatinine criteria	Urinary output criteria
1	Serum creatinine x 1.5 or serum creatinine rise of 0.3 mg/dl in 48 h	<0.5 ml/kg/h for 6 h
2	Serum creatinine x 2	<0.5 ml/kg/h for 12 h
3	Serum creatinine x 3 or serum creatinine ≥4 mg/dl or renal replacement therapy	<0.3 ml/kg/h for 24 h or anuria for 12 h

KDIGO, Kidney Disease: Improving Global Outcomes [6]Plasma neutrophil gelatinase-associated lipocalin (NGAL) >150 ng/ml;At least one of the following conditions: a) severe sepsis; b) use of catecholamines (norepinephrine or epinephrine >0.1 μg/kg/min); c) refractory fluid overload (worsening pulmonary edema, PaO2/FiO2 < 300 mmHg and/or fluid balance >10 % of body weight); and d) development or progression of non-renal organ dysfunction (Sequential Organ Failure Assessment (SOFA) score ≥2);Age between 18 and 90 years; andIntention to provide full intensive care treatment for at least 3 days.

### Exclusion criteria

The exclusion criteria are as follows:Pre-existing chronic kidney disease not requiring RRT (GFR <30 ml/min);Previous RRT;AKI caused by permanent occlusion or surgical lesion of the renal artery;AKI caused by glomerulonephritis, interstitial nephritis or vasculitis;AKI caused by postrenal obstruction;Hemolytic-uremic syndrome/thrombotic thrombocytopenic purpura;Pregnancy;Prior kidney transplantation;Hepatorenal syndrome;AIDS with a CD4 count of <0.05 x 10E/l;Hematologic malignancy with neutrophils of <0.05 x 10E/l;No hemofiltration machine free for use at the moment of inclusion; andParticipation in another interventional clinical trial.

### Enrolment

Enrolment began in August 2013. Prior to being randomized into the study, the trial coordinators obtain consent for participation in the study (see Ethics and consent). Assuming all inclusion criteria are fulfilled and no exclusion criteria are met, each patient receives a study identification number and treatment allocation at enrolment. Patients are randomized in a 1:1 ratio to one of the two treatment arms using a computerized system. Randomization is stratified by SOFA Cardiovascular organ Failure Score (0–2 vs. 3–4) and by the presence or absence of oliguria. The randomization day is day 0.

### Treatment arms

Early initiation of RRT will be initiated at stage 2 of the KDIGO classification within 8 hours:Urine output <0.5 ml/kg/h for ≥12 h; and/orTwo-fold increase of the serum creatinine level compared to the baseline value.

Late initiation of RRT will be initiated when stage 3 of the KDIGO classification (not later than 12 hours after achieving stage 3) is achieved:Urine output <0.3 ml/kg/h for ≥24 h; and/or > Three-fold increase of the serum creatinine level compared to the baseline value; and/orSerum creatinine of ≥4 mg/dl with an acute increase of at least 0.5 mg/dl within 48 hours.

Or if any of the following absolute indications for RRT are present:Urea serum levels >100 mg/dl;Potassium serum levels >6 mmol/l and/or ECG abnormalities;Magnesium serum levels >4 mmol/l;Urine production <200 ml/12 h or anuria (without diuretics, according to the KDIGO recommendations); andOrgan edema in the presence of AKI resistant to diuretic treatment (one attempt with loop diuretics prior to randomization).

After enrolment, ELAIN investigators are responsible for the catheter insertion and the initiation of RRT (see Additional file 1). Daily visits will be performed to ensure adherence to the protocol. Hemodynamic, pulmonary, inflammation, renal and laboratory data will be documented. Education to ensure proper implementation of the study protocol was done prior to starting enrolment. Project manager and trial investigators conduct monthly conferences to monitor all aspects of the protocol.

### Patient management

All patients receive standard intensive care therapy. As no pharmacological therapy for AKI exists, the management of AKI remains primarily supportive, with renal replacement therapy serving as a cornerstone of therapy for patients with severe kidney injury. None of the patients in both groups (‘early’ and ‘late’ groups) are exposed to additional risks.

The patient’s primary physicians determine the remainder of patient management, consistent with established best practices for the management of critically ill patients (e.g. use of diuretics, application of fluids). Measuring central venous pressure and cardiac output is performed in all patients. These co-interventions are not standardized, but they are recorded and will be analyzed after finishing the trail. As this is a prospective randomized trial, there should not be any differences between the groups. Further treatment rules are described in Additional file 1.

### Outcomes

The primary endpoint is overall survival in a 90-day follow-up period. If the difference in overall survival is significant, the treatment effect will be estimated by means of the 90-day all-cause mortality rate in both treatment groups.

Secondary outcomes include:Overall survival in a 28-day and 60-day follow-up period;Overall survival in a 1-year follow-up period;Clinical evidence of organ dysfunction (daily SOFA scores while in the ICU);Recovery of renal function as defined in the KDIGO guidelines [6];Requirement of haemodialysis after day 28 and day 60;Duration of renal support;ICU and hospital length of stay; andMarkers of inflammation, oxidative stress, cellular hypoxia and coagulation.

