### Secondary and tertiary outcome analyses

Statistical analysis of the pre-specified secondary endpoints will be performed with descriptive and inductive statistical methods. Survival data will be described by Kaplan–Meier plots and survival distributions will be compared using the log-rank test. Ordinal scores and non-normally distributed metric measures will be analyzed using non-parametric methods, including calculation of the median and quartiles and comparison of distributions using the Mann–Whitney U test. In case of normally distributed metric measures parametric methods will be used, including calculation of the mean and standard deviation and comparison of distributions using Student’s t-test. Binary data will be presented by contingency tables and rates will be compared using the Chi-squared test. Secondary and tertiary outcome analyses are considered not to be confirmatory. The *p* values are regarded noticeable in case *p* ≤0.05. No adjustment for multiple testing will be performed. Therefore, an overall significance level is not determined and cannot be calculated.

Additional exploratory analyses will include model-based analyses, subgroup analyses and safety analyses. In safety analyses, all study patients will be included (safety population).

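### The daily SOFA outcome keeps its renal item, which RRT itself can change, so an early between-arm difference can partly reflect the randomised treatment and not organ function

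*Protocol article*

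**What the plan says.** The Outcomes section names organ dysfunction as a secondary outcome, measured as "Clinical evidence of organ dysfunction (daily SOFA scores while in the ICU"). No item is left out, and nothing is said about scoring on days when a patient receives RRT. Under Secondary and tertiary outcome analyses, ordinal scores are summarised by median and quartiles, with "comparison of distributions using the Mann–Whitney U test". That section also calls these analyses non-confirmatory and treats p ≤ 0.05 only as noticeable.

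The arms differ in RRT exposure by design. The Fig. 1 legend says: "In the ‘early’ group, RRT will be initiated immediately after randomization, whereas initiation of RRT in the ‘late’ group will be started only after" stage 3 or an absolute indication. The Treatment arms section gives the windows: "Early initiation of RRT will be initiated at stage 2 of the KDIGO classification within 8 hours" and "Late initiation of RRT will be initiated when stage 3 of the KDIGO classification (not later than 12 hours after achieving stage 3) is achieved". Some late patients may never start: "Patients randomized to ‘late’ but never reaching stage 3 will remain in the ‘late’ group for purposes of analysis".

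Elsewhere the article handles SOFA by organ system. One entry condition is "development or progression of non-renal organ dysfunction (Sequential Organ Failure Assessment (SOFA) score ≥2"), and "Randomization is stratified by SOFA Cardiovascular organ Failure Score (0–2 vs. 3–4) and by the presence or absence of oliguria".

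**The concern.** SOFA has six items of 0 to 4 points, 24 in all, and one is renal. That item is read from creatinine or urine output, both of which the article's Background calls functional markers. Once a patient is on RRT, a lower creatinine shows clearance by the machine as well as any kidney recovery. On the first ICU days most of the early arm should be on RRT, and at least part of the late arm should not. The renal item can then separate the arms while the heart, lungs, liver, brain, coagulation and native kidney are the same in both.

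What is at stake is how one secondary result is read. The Discussion suggests that early RRT might limit both kidney and non-kidney injury. A difference in total SOFA would naturally be taken as support for that, although part of it could come from how the score is built.

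**Working it through.** **1. The plan's own figures.** The article states no SD, expected difference or sample size for SOFA, so there is no SOFA figure to reproduce. The trial's size rests on deaths: 106/0.46 = 230.4, taken as 230 evaluable patients, and 230/0.90 = 255.6, rounded up to 256 recruited. SOFA does not enter, so nothing here changes these figures.

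**2. Can the renal item follow allocation?** The article does not state a convention for RRT days. Two are possible:

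- *Scored from the measured values.* Clearance lowers creatinine, so the item can fall in the arm with more RRT.
- *RRT scored as maximum renal failure.* The item becomes 4 when RRT starts, so it rises in the arm with more RRT.

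The sign differs, but in both cases the treatment acts on the score. Fixing the convention settles the direction and does not remove the dependence.

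**3. What mean shift would result?** Let d be the change in the item for a patient whose item is altered by RRT that day, and q the difference between arms in the proportion of such patients. The mean shift is δ = q × d.

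- d = 1, q = 0.5: δ = 0.5.
- d = 1, q = 1: δ = 1. This needs every early patient affected and no late patient.
- d = 2, q = 0.5: δ = 1.
- d = 2, q = 1: δ = 2.

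Two features of the trial reduce q. Entry is possible on urine output alone, and an item driven by low urine output does not improve when creatinine is cleared. The late arm also receives RRT at stage 3 or on an absolute indication, in a population chosen to be at high risk of needing it. The article gives no value for q or d.

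**4. Illustration.** Assumptions, none from the article: 100 scored patients per arm on a given day, SD of total SOFA 4 (range 3 to 5), no true effect on any organ, two-sided 5% level, and a normal approximation standing in for the Mann–Whitney test.

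SE = SD × √(2/n) = 4 × √(2/100) = 0.566

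P(p ≤ 0.05) = Φ(δ/SE − 1.96) + Φ(−δ/SE − 1.96)

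| Mean shift δ | δ/SE at SD 4 | SD 4 | SD 3 | SD 5 |
|---|---|---|---|---|
| 0.25 | 0.44 | 7% | 9% | 6% |
| 0.5 | 0.88 | 14% | 22% | 11% |
| 1 | 1.77 | 42% | 65% | 29% |
| 2 | 3.54 | 94% | >99% | 81% |

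With 115 per arm (half of 230), SD 3 to 5 gives 12–24% for 0.5 points, 33–72% for 1 point and 86–99.9% for 2 points. The result depends mainly on δ, which is unknown.

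**The case against.** The strongest reply is that this is one exploratory outcome among several, and that the article does not say only the total will be compared. It speaks of daily scores, and the scoring rule and choice of summary may sit in a full protocol or analysis plan that is not shown. Renal recovery, haemodialysis requirement and duration of renal support are separate secondary outcomes, so a reader can set a SOFA difference beside the renal course. All of this limits the weight of the point. It does not remove it: the outcome as listed excludes nothing, and a scoring rule held elsewhere would leave the treatment inside the score.

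Four stronger readings are tempting and are not supported.

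- *That the SOFA comparison has a false-positive rate of 42% or 94%.* Those figures follow from assumed mean shifts of 1 and 2 points. Oliguria-driven scores and late-arm RRT could make the shift much smaller; 0.25 points gives about 7%. The article also claims no error control for secondary outcomes.
- *That the bias favours early RRT.* The sign depends on a convention the article does not state. Nor is variation between sites the issue, since this is a single-centre trial.
- *That the plan contradicts itself by using non-renal dysfunction at entry.* Every candidate already has stage 2 kidney injury, so counting the kidney there would add little. The criterion shows that the authors had the distinction available, not that the outcome breaks it.
- *That the outcome fails a stated hypothesis about non-renal organs.* The Discussion names kidney and non-kidney injury together, and the formal aims attach no such hypothesis to SOFA.

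**Conclusion.** The point holds in a limited form. As listed, the organ-dysfunction outcome includes an item that the randomised treatment can change directly, so a between-arm difference in total SOFA on early ICU days can partly reflect RRT exposure. This rests on the instrument's renal item being scored from creatinine or urine output, and on the exposure contrast that the article sets up.

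Neither size nor direction can be settled from the article. At 100 per arm and SD 4, the chance of a noticeable result with no true effect runs from close to the nominal 5% for a small shift to about 94% for 2 points. The renal item is 4 of 24 points, so a total-score difference could still partly be genuine. The primary survival endpoint, the global alpha of 0.05, the 106 deaths and the 256 patients are untouched. This is a cheap improvement to a non-confirmatory outcome, not a threat to the trial's main conclusion.

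**What to change.** In the Outcomes section, define organ dysfunction as the daily non-renal SOFA score in the ICU: five items, range 0 to 20. Report the renal item separately with RRT status for that day, as description only, and state how it is scored on RRT days. Tabulate total SOFA as supportive. SOFA in the baseline risk model can stay as it is, because it is taken before randomisation.

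The cost is a line in the outcome definition and a re-summation of items that the total score already requires. No planned number changes, and renal information is kept through the existing renal outcomes. The downside is that the main score is slightly less comparable with papers reporting total SOFA, which the supportive table largely covers.
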